**Methods::**

This is a prospective nonrandomized controlled study. A sample of 152 participants will be assigned to 2 groups in a 1:1 ratio. The participants in the control group will receive conventional Valsalva and Toynbee maneuvers, while those in the experimental group will be given additional self-acupressure therapy. The acupoints used will be TE17 (Yifeng), TE21 (Ermen), SI19 (Tinggong), and GB2 (Tinghui). The Modified Teed Classification, symptoms of MEB, and overall ear discomfort levels will be assessed. Data will be analyzed using the Chi-Squared test or *t* test.

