### Sample size calculation

2.4

According to a previous study on the effect of dried salted plum for HBOT induced otalgia,^[22]^ moderate to severe otalgia was present in 0.0% (0 of 53) of those consuming a dried salted plum vs 10.8% (4 of 37) of the control group (*P* = .026). Anticipating a power of 80% (1 – β = 0.8), statistical significance (α = 0.05) of 95%, and a dropout rate of 10%, a total of 76 participants for each group will be required in this study (https://clincalc.com/stats/samplesize.aspx).

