### Outcome measurements

2.6

The primary outcome measurement is the presentation of the tympanic membrane recorded according to the Modified Teed Classification, with grades from 0 to 5, where Grade 0 indicates symptoms with no ontological signs of trauma; Grade 1 indicates injection of the tympanic membrane; Grade 2 indicates Grade 1 plus injection plus mild hemorrhage within the tympanic membrane; Grade 3 indicates gross hemorrhage within the tympanic membrane; Grade 4 indicates free blood in the middle ear, evidenced by blueness and bulging; and Grade 5 indicates perforation of the tympanic membrane.

The secondary outcomes are symptoms of MEB and the overall ear discomfort levels. Recorded symptoms of MEB include feeling pressure in the ears, ear pain, headache, dizziness, vertigo, tinnitus, and hearing loss. The symptoms of MEB and the overall ear discomfort levels will be estimated using a 10-cm visual analogue scale with anchor points of 0 (no discomfort) and 10 (maximum discomfort) at the same time as the primary outcome measure. A higher score will indicate a higher level of discomfort during HBOT. The outcomes will be measured at baseline before the first HBOT, after the first 5 consecutive treatments of HBOT, and after each 10 treatments of HBOT until the twentieth HBOT.

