### Statistical analysis

2.7

Quantitative variables, presented as mean ± SD, will be analyzed by the Student *t* test. Qualitative variables, expressed as a number (percentage), will be analyzed using the Chi-Squared test. All analyses will be performed in SPSS software. Differences will be considered statistically significant at *P* < .05.

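### The secondary VAS scores are read repeatedly, but the only method named for them is a Student t test with no per-person summary; a mixed model would use the readings better

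*Protocol article*

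**What the plan says.** Section 2.6 makes the symptom scores and overall ear discomfort secondary outcomes: "The symptoms of MEB and the overall ear discomfort levels will be estimated using a 10-cm visual analogue scale". Readings are taken at baseline and then "after the first 5 consecutive treatments of HBOT, and after each 10 treatments of HBOT until the twentieth HBOT". This can be read as treatments 5, 10 and 20 (three post-baseline readings), or as 5 and then 10 treatments later (two, since a further 10 would pass the twentieth).

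Section 2.7 gives one method for scores of this kind: "Quantitative variables, presented as mean ± SD, will be analyzed by the Student" t test. The abstract says the same: "Data will be analyzed using the Chi-Squared test or" t test. Neither place names a repeated-measures model, a baseline adjustment, a main time point or a per-person summary.

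Two other statements bear on the point. Section 2.4 allows for 10% dropout. The Discussion describes MEB as a major reason why patients discontinue treatment.

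**The concern.** A t test between groups takes one value per person. If that value is the reading at a single visit, three things follow.

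- The person's other readings do not contribute, although they have been collected and carry information on the same question.
- A participant who stops after treatment 5 drops out of every later comparison. If discomfort itself leads people to stop, those who remain at later visits are a selected group, and the selection may differ between the groups.
- With two or three tests per scale, nothing says which one answers whether discomfort was reduced.

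At stake are the precision and interpretability of the secondary discomfort results.

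**Working it through.** **The plan's own figure.** Section 2.4 uses 4/37 (10.8%) against 0/53 (0%), 80% power and alpha 0.05. The two-sided comparison of two proportions with pooled variance and no continuity correction gives 68 per group. Allowing for 10% dropout, 68/0.90 = 75.6, which rounds up to 76. The stated 76 per group is reproduced, and it does not involve the VAS. The 68 evaluable per group is carried forward.

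**Assumptions, because the article gives no VAS figures.** Equal variance at each visit, a common within-person correlation rho of 0.3 to 0.8, complete readings, the same true effect at each visit, and an illustrative effect of 0.4 SD.

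**Formula.** The mean of k readings has variance (1 + (k - 1) x rho)/k relative to one reading. The equivalent number per group is 68 divided by that factor. Power is that of a two-sided t test at 0.05 with 68 per group and a standardised effect of 0.4 divided by the square root of the factor. With one reading, power is 63.9%.

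| k | rho | variance factor | equivalent n per group | power at 0.4 SD |
|---|---|---|---|---|
| 2 | 0.3 | 0.65 | 105 | 82% |
| 2 | 0.5 | 0.75 | 91 | 76% |
| 2 | 0.7 | 0.85 | 80 | 71% |
| 2 | 0.8 | 0.90 | 76 | 68% |
| 3 | 0.3 | 0.53 | 128 | 89% |
| 3 | 0.5 | 0.67 | 102 | 81% |
| 3 | 0.7 | 0.80 | 85 | 73% |
| 3 | 0.8 | 0.87 | 78 | 70% |

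The factor is below 1 for every rho below 1, so under these assumptions the direction does not depend on the choice of rho. The size does.

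**Adding baseline.** With three readings and the same correlation to baseline, the factor becomes (1 + 2 x rho)/3 - rho squared: 0.44, 0.42, 0.31 and 0.23 at rho 0.3, 0.5, 0.7 and 0.8. This is optimistic. Baseline is taken before any chamber session, so scores may lie near zero and predict little. The conclusion does not rely on it.

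**When the effect is not similar at each visit.** With three readings and a 0.4 SD effect at m of them, the averaged effect is 0.4 x m/3.

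- Effect at one visit: power of the averaged contrast is 19% (rho 0.3) to 14% (rho 0.7).
- Effect at two visits: 56% (rho 0.3) to 41% (rho 0.7).

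Both are below the 64% of a t test at an affected visit.

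**The case against.** The best defence is that section 2.7 does not say which value enters the t test. A reader might infer that the plan commits to testing visit by visit. The text does not say so: a t test on each person's post-baseline mean, or on another summary, is equally compatible with it. This stands. The gains tabulated above are those of exactly such a t test on the mean, so they come from using all the readings and not from the mixed model as such.

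A second defence is that a condensed article leaves the time point and the handling of missing readings to fuller documents. This stands in part. Silence on those details is no fault, but the article does name a method, twice, and that method by itself makes no use of the repeated structure set out in section 2.6.

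Third, the size rests on inputs from outside the article. This also stands. The 89% needs three readings, rho 0.3, an equal effect throughout and no missing readings; with two readings and rho 0.8 the gain is only from 64% to 68%.

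Fourth, a mixed model has limits of its own. Its missing-at-random assumption is weaker than what visit-wise complete-case tests need, but it may fail if discomfort after the last reading is what makes people stop. Section 2.3.1 does not require a 20-treatment prescription, so some late readings may never be due. And since the groups are nonrandomized and recruited in different periods (section 2.2), a narrower interval does nothing about period or selection bias. All of this stands and limits what the change can achieve.

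**Conclusion.** The point holds in limited form. Repeated VAS readings are paired with a method that takes one value per person, and no summary is named. If the test is applied to single visits, precision is lost and participants who stop early are left out of later comparisons. For rho between 0.3 and 0.8 and a similar effect at each visit, the post-baseline mean has about 0.53 to 0.90 of the variance of a single reading. At 0.4 SD and 68 per group, that is power of about 68-89% against 64%. The correlation, the effect size and the constancy of the effect are all assumptions.

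Two stronger conclusions are not supported. A reader might infer that the t test is invalid; at a single visit it is a legitimate but less efficient comparison of those still observed. A reader might also infer that the sample size is undermined; it rests on a binary otalgia rate, reproduces exactly, and is untouched. This is a worthwhile improvement to secondary analyses.

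**What to change.** For the VAS scores, replace the t test with one linear mixed model per scale. Use all post-baseline readings as outcomes, with group, visit, group-by-visit and baseline VAS as fixed effects and an unstructured within-person covariance. Report the visit-averaged group difference with its 95% CI, and the visit-specific differences alongside. State whether the post-baseline readings number two or three, and how a visit beyond the end of a participant's prescribed course is treated, as distinct from a missed reading. If a simpler analysis is preferred, a t test on each person's post-baseline mean, named in advance, would recover much of the precision.

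The cost is a change of wording and slightly more analysis in SPSS, the software already planned, with no new data or participants. The price is lower power for the averaged contrast when the effect is confined to one visit (14-19% in the case above), which is why the visit-specific differences should be reported too. The report should say plainly that the model does not remove bias from the nonrandomized, separate-period recruitment.

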**Objectives::**

This study aims to evaluate the efficacy of self-acupressure for preventing and reducing the degree of MEB associated with HBOT.

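### Neither test named in section 2.7 suits the ordered 0–5 Teed grade, and the likeliest reading, a 2×6 chi-squared test, gives up much of the power to show milder barotrauma

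*Protocol article*

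**What the plan says.** Section 2.6 (Outcome measurements) defines the primary outcome as the state of the tympanic membrane, "recorded according to the Modified Teed Classification, with grades from 0 to 5". The grades run from no visible sign of trauma up to perforation, so they are ordered. The Objectives paragraph of the abstract states the aim: to "evaluate the efficacy of self-acupressure for preventing and reducing the degree of MEB associated with HBOT".

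Section 2.7 (Statistical analysis) names two tests. Quantitative variables, given as mean and SD, go to the Student t test. For the rest, "Qualitative variables, expressed as a number (percentage), will be analyzed using the Chi-Squared test". The abstract's Methods paragraph gives the same pair: "Data will be analyzed using the Chi-Squared test or" the t test.

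The secondary outcomes are scores: "The symptoms of MEB and the overall ear discomfort levels will be estimated using a 10-cm visual analogue scale". The Teed grade is therefore the one graded categorical outcome, and on its face it falls under the chi-squared sentence. Section 2.7 names no trend, rank or ordinal method and gives no cut-point for the grades.

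**The concern.** Whether the degree of MEB is reduced is a question about order. A Pearson chi-squared test on a table of two groups by six grades spends 5 degrees of freedom on any difference in pattern, and returns the same P value if the grade labels are shuffled. It gives no estimate of a shift in severity. High grades are likely to be rare, so many columns will be thinly filled.

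The other named test, a t test on the grade, does use the order. But it treats the step from injection to mild haemorrhage as equal to the step from free blood to perforation.

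At stake is a consistent move toward lower grades in the acupressure group that the planned test fails to detect.

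**Working it through.** **1. The plan's own sample size (section 2.4).** Inputs: 10.8% against 0.0%, 80% power, alpha 0.05 (taken as two-sided), 10% dropout. The mean rate is 0.054.

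n = [1.960·√(2·0.054·0.946) + 0.842·√(0.108·0.892)]² / 0.108² = (0.626 + 0.261)² / 0.01166 ≈ 67.6, so 68 per group.

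With dropout, 68/0.90 = 75.6, so 76, which is the stated figure. The calculation is for a binary otalgia rate, not for the Teed grade. The evaluable number used below is 68 per arm.

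**2. Cost of the degrees of freedom, with no assumed grade distribution.** A 1-df test with 80% power at two-sided 0.05 has noncentrality (1.960 + 0.842)² ≈ 7.85. A 5-df chi-squared test with the same noncentrality has power 55.5%.

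**3. Simulated power at 68 per arm.** The article gives no grade distribution, so two are assumed for the control arm (grades 0 to 5):
- A: 60/22/10/5/2/1%
- B: 80/10/5/3/1/1%

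The effect is one common odds ratio (OR) for being at or below each grade. At OR 2.5, grade 0 in A rises from odds 0.60/0.40 = 1.5 to 3.75, that is 78.9%. In B it rises from odds 4 to 10, that is 90.9%.

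| Control | OR | 2×6 chi-squared | t test on grade | Chi-squared, 0 vs ≥1 | Rank test |
|---|---|---|---|---|---|
| A | 2 | 25% | 40% | 47% | 47% |
| A | 2.5 | 41% | 61% | 69% | 70% |
| A | 3 | 56% | 74% | 81% | 82% |
| B | 2 | 13% | 25% | 31% | 31% |
| B | 2.5 | 18% | 37% | 44% | 45% |
| B | 3 | 26% | 46% | 54% | 55% |

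Repeat simulations agree within about 3 points. Over four other assumed distributions, from 30% to 89% of controls at grade 0, and odds ratios of 2 to 3, the 2×6 test loses about 13 to 32 points to the rank test.

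**4. Sparse cells in the 2×6 table at OR 2.5.**
- A: grade 3 or above is 8% in controls. Odds of grade 2 or below are 0.92/0.08 = 11.5, and 11.5 × 2.5 = 28.75, leaving 3.4% in the other arm. The mean is 5.7%, and 68 × 0.057 ≈ 3.9. Grades 3, 4 and 5 share about 3.9 expected patients per arm, so all three columns fall below 5.
- B: grade 2 or above is 10% in controls. Odds of grade 1 or below are 9, and 9 × 2.5 = 22.5, leaving 4.3%. The mean is 7.1%, and 68 × 0.071 ≈ 4.8. Grades 2 to 5 share that, so all four columns fall below 5.

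With no effect, the 2×6 test rejects in about 3.4% (A) and 2.8% (B) of trials, against 4.8% and 5.1% for the rank test.

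**5. The 2×2 table at the planning rates.** The expected event count is 68 × 0.108 / 2 = 3.67 per cell. By exact enumeration at 68 per arm and a common rate of 5.4%, the uncorrected chi-squared test has type I error 4.8% and Fisher's exact test 1.4%. At 10.8% against 0%, power is 94% and 76%.

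**The case against.** The strongest reply is that the 2×6 layout is inferred. Section 2.7 is a general rule, and no sentence assigns a test to the Teed grade. The sample size rests on a binary rate, which might suggest cutting the grade at 0 against 1 or more. Alternatively, the grade might be scored and compared by t test. On the first alternative almost no power is lost under A and B. On the second the loss at OR 2.5 is 9 points (70 − 61) and 8 points (45 − 37). A condensed article may also leave table layout to a fuller document.

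Much of this stands. A reader might infer that the protocol commits itself to a 2×6 test and that the full loss is certain. The text does not support that, and the 2×6 figures must be read as conditional. What the reply does not remove is that the article is not silent: it names its tests, and each reading leaves a defect. The 2×6 test ignores order. The t test assumes equal steps. The binary cut says nothing about severity above the cut, and it also loses power when grades are widely spread (74% against 83% at OR 2.5 with 30% of controls at grade 0).

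A reader might also infer that a 2×2 chi-squared test is unreliable at an expected count of 3.67 and should give way to Fisher's exact test. Step 5 shows the reverse. The uncorrected test holds its level, while Fisher's would take power below the planned 80%.

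Two smaller replies are fair. Percentages by group would show the direction of a shift even though the test does not. And a conservative test adds no false-positive risk.

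**Conclusion.** The point holds as a fault in the choice of method: neither named test suits an ordered primary outcome in a trial that aims to reduce severity. On the most natural reading, power at OR 2.5 falls from about 70% to 41%, or from 45% to 18%. On the other two readings the loss under these distributions is 8 to 9 points or close to none.

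The sizes rest on 68 evaluable per arm, on grade distributions that the article does not supply, and on a proportional-odds shift. The 2×6 test did worse than the rank test in every distribution tried. The result would not be invalid, so this is a recommended change, not a fatal one. The sample size of 76 per group is not put in question here, and neither is the uncorrected chi-squared test for a binary comparison.

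**What to change.** State in section 2.7 that the Modified Teed grade is compared between groups by the Wilcoxon rank-sum test or by proportional-odds ordinal regression, and that the common odds ratio is reported with its 95% CI. The uncorrected 2×2 chi-squared test may stay for any comparison of grade 0 against 1 or more.

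The cost is one sentence, with no new data and no change in sample size. The small downside is that a single odds ratio leans on the proportional-odds assumption. It also has no finite estimate if every patient in one arm is grade 0, in which case the rank test still gives a P value.

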### Data monitoring

2.8

No data monitoring committee will be needed because self-acupressure is general practice and a noninvasive intervention. Nevertheless, adverse events such as subcutaneous hematomas or localized rash near the location of self-acupressure therapy will be monitored during the trial period.

## Discussion

3

MEB, one of the main common side effects of HBOT, is a major reason why patients discontinue HBOT. Although the Valsalva and Toynbee maneuvers are usually used to prevent symptoms of MEB associated with HBOT, many patients still experience ear discomfort during and after HBOT. The present study aims to evaluate whether additional self-acupressure in combination with the Valsalva and Toynbee maneuvers is more effective in preventing and reducing the discomfort caused by MEB than are the Valsalva and Toynbee maneuvers alone. Self-acupressure is a simple, noninvasive treatment that can be performed at any time, as opposed to acupuncture, which is invasive and can only be performed by trained physicians. If additional self-acupressure is proven more effective, patients may be more willing and feasible to complete the course of HBOT.

Acupressure, which originated in ancient China, is based on the theory of TCM and is closely associated with acupoint activation across the meridians, just as acupuncture is. Acupressure uses pressure to stimulate specific acupoints which can correct imbalances in the *Qi* through channels and subsequently treat diseases.^[16]^ The biochemical mechanism of acupressure involves the stimulation of acupoints that leads to complex neuro-hormonal responses, such as antiinflammation via the hypothalamic-pituitary-adrenocortical axis.^[16]^ In addition, acupressure mediates the nitric oxide signal, which is known to improve local microcirculation via cyclic guanosine monophosphate.^[16]^ Stimulation of acupoints near the ear may alleviate symptoms of MEB. In the present study, correct position and proper strength during self-acupressure will be important. One well-trained practitioner will educate the participants in the experimental group on additional self-acupressure therapy and confirm that the self-acupressure is correctly performed. The participants in the experimental group and those in the control group will be recruited in separate periods of time so as to avoid contact between the 2 groups of participants and thereby minimize the likelihood that the patients might learn about self-acupressure from one another while receiving HBOT in the same chamber.

In conclusion, the results of this study are expected to provide evidence on the efficacy of self-acupressure as a no cost, noninvasive self-management method for MEB associated with HBOT in addition to the Valsalva and Toynbee maneuvers.
